### Evaluating sample validity (RQ8)

One of the objectives of PQIP is to measure and report processes and outcomes from surgery for the purposes of quality improvement. While it is widely accepted that data from a non-random sample of patients within an institution may provide important information about reliability of processes and systems (Peden and Moonesinghe 2016), sampling of patient outcomes should be statistically and conceptually robust so as not to provide biased estimates. Clinical trials and cohort studies which have specific inclusion and exclusion criteria, or which require patient consent, can be criticised as non-representative (and therefore the findings are of limited generalisability) (Deaton and Cartwright 2018). A potential solution to this is to use administrative data to evaluate outcomes; however, in the UK, such data are limited to mortality, hospital readmission and length of stay.

We will address these issues through an evaluation of our sampling strategy using administrative data from Hospital Episode Statistics (HES). For included procedures, an anonymised extract of HES data will be requested from NHS Digital for each hospital. This will enable us to conduct sensitivity analyses comparing patient characteristics (for example age, comorbidity, socioeconomic status using the Index of Multiple Deprivation) and outcomes (mortality, hospital readmission, length of hospital stay) between patients included in PQIP and those who are not. We will do this at individual hospital level and at aggregate (national) level.

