### Limitations

The requirement for patient consent means that the sample may be biased. While this is of less importance for process measures which will be used to evaluate care quality, it is relevant when considering outcomes. We will mitigate this risk through comparison of the PQIP population to the total sample of patients undergoing PQIP included procedures using Hospital Episode Statistics (HES) data. This will enable us to undertake sensitivity analyses which will demonstrate what (if any) biases there are in our sampling.Similarly, our ambition to enable as many hospitals as possible to participate irrespective of local resourcing, means that some hospitals will attempt to recruit all patients who are potentially eligible, and some only a sample. We will again try to mitigate this risk through encouraging hospitals to recruit a random sample of patients and will compare the PQIP sample against the HES-defined population at local level as well.

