### Participants

All NHS hospitals which undertake any of the included procedures are eligible to participate. Hospitals are approached via the Royal College of Anaesthetists and its Health Services Research Centre, and via the National Institute for Health Research’s portfolio system. Patients aged 18 years or older undergoing planned major surgery (as defined by a list of index procedures requiring inpatient stay) will be eligible for recruitment and patient consent will be sought pre-operatively. Patient consent is required as the study seeks additional data to that collected as part of routine care (specifically the patient-reported outcome data). The consenting process is undertaken by staff locally trained and approved. The participant information provides detail on how data are collected, the request for patient reported data, and the linkage of hospital data with external databases (see below, dataset).

Hospitals may choose to recruit patients from all specialties or specify particular specialties where they wish to focus at local level. Each hospital is offered the opportunity to either approach all eligible patients for consent, or all patients within a particular specialty or plan to recruit between one and five patients per week, approaching patients for written consent based on a random sampling strategy. This will involve an eight-day rolling sampling cycle (i.e. for week one the first five patients starting on Monday morning, followed by the first five patients starting from Tuesday in week two, et cetera). If any of the first five patients approached decline to consent, then consecutive patients will be approached for consent until the target recruitment number has been achieved. Patients can choose to be withdrawn from the study at any time.

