## Discussion

PQIP has now been running for 4 years, and was paused for approximately one year during the Covid pandemic, both because elective surgery activity reduced substantially, and because clinical and research teams were diverted to support the emergency response. Review of data collected to that point and discussion with clinical teams has found that the random sampling approach was largely infeasible at hospital level. Therefore, a convenience sampling approach has been adopted by most sites. This further underlines the importance of our planned analyses to evaluate risk of bias in our patient selection and our results.

This also highlighted another challenge with our approach: the direct cost of participation in the study. Hospitals are incentivised to take part because the PQIP patient study is registered on the National Institute for Health Research’s portfolio of approved studies: therefore, sites are financially rewarded for recruiting patients. However, the costs of data collection and entry must be covered locally, and this is a significant challenge, which has limited both site participation and the number of patients recruited per site. Nonetheless, over 126 hospitals have taken part in the PQIP patient study so far, and over 35,000 patients have been recruited.

PQIP has also successfully collaborated with another research team to facilitate an NIHR funded randomised controlled trial to use the PQIP data collection platform and co-recruit into both studies (https://www.journalslibrary.nihr.ac.uk/programmes/hta/NIHR130573/#/) This approach to efficient trial design should bring benefit to patients, clinicians, researchers and provide excellent value for money.

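### Most sites now recruit by convenience, and the HES comparison meant to guard against selection neither checks nor corrects the POMS primary outcome or the complication rates

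*Protocol article*

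**What the plan says.** **Sampling.** Under Participants, a hospital may approach all eligible patients, approach all in one specialty, or recruit one to five a week, "approaching patients for written consent based on a random sampling strategy". Limitations names "encouraging hospitals to recruit a random sample of patients" as a way to reduce bias from uneven recruitment. The Discussion, written after four years of running, reports that "the random sampling approach was largely infeasible at hospital level" and that "a convenience sampling approach has been adopted by most sites". It then points to the planned bias analyses as the answer.

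**HES comparison.** Limitations promises a "comparison of the PQIP population to the total sample of patients undergoing PQIP included procedures". The RQ8 section says that "an anonymised extract of HES data will be requested from NHS Digital for each hospital", and that characteristics and three outcomes (mortality, readmission, length of stay) will be compared "between patients included in PQIP and those who are not", by hospital and nationally. The same section says that the sampling of outcomes ought to be robust enough to avoid bias, and that UK administrative data hold only those three outcomes.

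**Outcomes.** Under Dataset, the primary outcome is any POMS-defined morbidity on day 7. Clavien-Dindo complications are secondary, and failure to rescue is built on Clavien-Dindo grade II or above. The Descriptive statistics section reports outcomes both unadjusted and case-mix adjusted.

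**Linkage.** Dataset and Data management and linkage provide for patient-level linkage of participants to HES and ONS mortality data, using NHS number, date of birth, gender and postcode.

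**The concern.** RQ2 asks for national rates of complications, failure to rescue and mortality. An unweighted rate answers that only if those recruited resemble those eligible. With consent required and most sites recruiting by convenience, nothing in the design secures this, so the protection has to come from the analysis. The stated analysis describes differences between PQIP and HES, for outcomes that are not the primary one. If higher-risk patients are approached or consent less often, the published POMS rate is too low. The HES comparison might reveal the skew in age, comorbidity or deprivation, but nothing states what that would mean for the POMS rate. Unadjusted hospital rates have the same weakness, and selection may differ between hospitals. Meanwhile, a reader of Limitations or Participants alone would believe that random sampling is in force.

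**Working it through.** The article gives no figure on this point to reproduce: the target of 70,000 comes without inputs, and no sampling fraction or eligible-population rate is stated. The check has four steps.

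**1. Can the HES comparison be run, and do its two comparators conflict?** Let f be the fraction of eligible patients recruited, and p_in, p_out and p_total the rates in participants, non-participants and all eligible patients.

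- p_total = f·p_in + (1 − f)·p_out
- hence p_out = (p_total − f·p_in)/(1 − f)
- and p_in − p_total = (1 − f)(p_in − p_out)

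Linkage gives p_in for the HES outcomes, and the extract gives p_total. Non-participants follow by subtraction, with no flag on individual records. With assumed p_in = 1% and p_out = 2%, at f = 20%: p_total = 0.2 × 1% + 0.8 × 2% = 1.8%, and p_out = (1.8% − 0.2%)/0.8 = 2.0%. The total in Limitations and the non-participants in RQ8 are two views of one contrast.

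**2. Which outcomes does the comparison reach?**

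| Outcome | Held in HES/ONS for all eligible patients | Check or correction stated |
|---|---|---|
| Mortality, readmission, length of stay | Yes | Direct comparison |
| POMS morbidity, day 7 (primary) | No | None |
| Clavien-Dindo complications, and failure to rescue built on them | No | None |

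**3. What could this cost? (All inputs assumed.)** Two risk strata: 30% of eligible patients are high risk, with morbidity 30% against 10% in the rest. True rate: 0.3 × 30% + 0.7 × 10% = 16.0%.

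| Participation, high v low risk | High-risk share of sample | Unweighted rate | Bias |
|---|---|---|---|
| 50% v 50% | 30.0% | 16.0% | 0 |
| 30% v 50% | 0.09/(0.09 + 0.35) = 20.5% | 14.1% | −1.9 points |
| 20% v 50% | 0.06/(0.06 + 0.35) = 14.6% | 12.9% | −3.1 points |

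Random-error half-width at 16%: 1.96 × √(0.16 × 0.84/35,000) = 0.38 points, or 0.27 points at 70,000. Further recruitment shrinks the second quantity and leaves the first alone.

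**4. What would weighting do?** If selection acts only through the recorded strata, applying the HES mix to the stratum rates gives 0.3 × 30% + 0.7 × 10% = 16.0% in every row. The price, by Kish's approximation (mean squared weight over squared mean weight, weights being 1/participation):

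- 30% v 50%: 5.455/2.273² = 1.056, so intervals are √1.056 = 1.03 times as wide (0.38 becomes 0.39 points).
- 20% v 50%: 7.073/2.439² = 1.189, so √1.189 = 1.09 times (0.42 points).

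With more covariates, or within small hospitals, weights vary more and the price rises.

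**The case against.** Four points on the other side deserve weight.

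- **The problem is disclosed.** The Discussion states the shift to convenience sampling, and Limitations lists consent bias and uneven site recruitment. This stands, but disclosure does not correct a rate, and the Discussion relies on analyses that do not reach the primary outcome.
- **Outcomes are also reported risk-adjusted**, for age, gender, operation type and P-POSSUM and SORT variables, with deprivation a candidate. This largely overlaps the factors one would weight on, so a gain for adjusted hospital comparisons (RQ3) is not shown. It does not rescue the national rates: adjusting among recruits does not restore the eligible population.
- **The article is condensed.** A weighting method may sit in the full protocol or SAP, so its absence is weak evidence by itself. The mismatch between the sampling sections and the Discussion does not depend on that.
- **The size is assumed.** This stands in full.

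Two stronger readings are tempting. A reader might infer that an anonymised extract cannot separate participants from non-participants, so the RQ8 comparison is impossible. The article does not support this: participants are linked to HES at patient level, and subtraction gives the rest. A reader might also infer that a comparator containing the participants hides bias where recruitment is high. It does not: participants minus total is exactly the bias of the PQIP estimate, and it shrinks with f because the bias itself shrinks.

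**Conclusion.** The point holds in a limited form. Most sites, though not all, recruit by convenience. The stated HES comparison is feasible and useful for mortality, readmission and length of stay, but it neither checks nor corrects POMS morbidity or Clavien-Dindo complications. The national rates for those outcomes and the unadjusted hospital rates therefore carry whatever selection exists, contrary to the article's own aim of avoiding biased estimates. It would be wrong to say that every outcome rate is unprotected: three outcomes can be checked directly, and RQ9 uses administrative data on enrolled and non-enrolled patients.

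No size can be read from the article. The illustration (0 to −3.1 points on a true 16.0%) rests wholly on assumed strata, rates and participation, and the direction is assumed too. It shows only that modest differential participation can outweigh a sampling error of 0.38 points. The matter is worth acting on, but it does not invalidate the study.

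**What to change.** 1. State a sensitivity analysis that post-stratifies or inverse-probability weights the POMS and complication rates to the HES eligible population, on age, comorbidity, deprivation and procedure, within hospital where numbers allow. Take these variables from HES for participants and for the eligible population, so that coding differences are not mistaken for selection. Report weighted beside unweighted rates.
2. For mortality, readmission and length of stay, print the HES rate for all eligible patients next to the PQIP rate. Applying the same weights to these outcomes also shows whether weighting closes a gap whose true size is known.
3. Say how participants are identified or subtracted in the extract, and name one comparator in Limitations and RQ8.
4. Reconcile Limitations and Participants with the Discussion: random sampling was planned, and convenience sampling is what most sites do.

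**Cost.** Extra analysis on data already being requested, and somewhat wider intervals (3% to 9% in the illustration, more with finer strata). Weighting corrects only for factors that HES records. Selection on frailty or willingness to take part within strata would remain, and the report should say so.

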### Research questions

What is the level of compliance with evidence-based structures and processes for patients undergoing major surgery?What are the rates of complications, failure to rescue (FTR), short- and long- term mortality in patients undergoing major planned surgery in NHS hospitals?How do the rates of adverse outcomes vary over time and between institutions?Are there structural or process related predictors of these adverse outcomes?What is the relationship between different measures of postoperative outcomes (e.g. different measures of morbidity; short and longer-term outcomes, health-related quality of life and disability)?What is the validity and predictive performance of previously published risk prediction models for different perioperative outcomes in the PQIP population?Can existing risk models be improved, or more parsimonious versions developed to support temporally responsive risk adjustment and clinically useful risk evaluation?How representative is the sample of patients recruited to PQIP of the total cohort of patients undergoing potentially eligible procedures in PQIP hospitals?Is there an outcome benefit to hospital and/or patient involvement in PQIP which can be differentiated from secular variation?Can quality of care be improved through a theoretically underpinned complex intervention supporting the use of data for improvement at local level, and do patient outcomes also improve?

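### RQ8 compares a hospital's PQIP patients with all its other included procedures, so where recruitment is limited to chosen specialties it cannot separate specialty coverage from patient selection within specialty

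*Protocol article*

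**What the plan says.** All references are to the protocol article.

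- **Participants.** "Hospitals may choose to recruit patients from all specialties or specify particular specialties where they wish to focus at local level". The recruitment options are to approach every eligible patient, "or all patients within a particular specialty or plan to recruit between one and five patients per week".
- **Research questions.** RQ8 asks how well the sample represents "the total cohort of patients undergoing potentially eligible procedures in PQIP hospitals".
- **Evaluating sample validity (RQ8).** "For included procedures, an anonymised extract of HES data will be requested from NHS Digital for each hospital". Characteristics and outcomes are then compared "between patients included in PQIP and those who are not". The work is described as "comparing patient characteristics (for example age, comorbidity, socioeconomic status using the Index of Multiple Deprivation", with mortality, readmission and length of stay as outcomes. On the level of comparison: "We will do this at individual hospital level and at aggregate (national) level".
- **Limitations.** Consent and partial recruitment are named as sources of bias. The comparison with the HES population is offered as the mitigation, through "sensitivity analyses which will demonstrate what (if any) biases there are in our sampling".
- **Discussion.** Most sites have moved to convenience sampling, and these planned analyses are said to matter all the more for judging bias in patient selection.
- **Temporal and between-hospital variation in outcomes (RQ3).** Risk adjustment includes operation type.

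**The concern.** Take a hospital that recruits from one specialty only. Its patients outside PQIP are of two kinds: those in the recruiting specialty who were not approached or declined, and those in other specialties whom the hospital never set out to recruit. The RQ8 contrast pools the two kinds.

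A difference can therefore come from the hospital's choice of specialty, from selection of patients within it, or from both, and one contrast cannot tell them apart. The distinction matters for RQ3. Operation type is in the risk adjustment there, so a difference in specialty mix is at least partly dealt with. Recruiting fitter patients within the same procedure is not, unless the measured risk factors capture it. With convenience sampling at most sites, that second kind of selection is a live possibility, and it is the one the Limitations and Discussion need RQ8 to reveal.

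**Working it through.** The article gives no figure for RQ8, so there is nothing to reproduce. The check is whether the stated contrast can recover selection within specialty.

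**Set-up (assumed).** A hospital has two specialties and recruits only from A.
- s = A's share of the hospital's included procedures
- r = fraction of A recruited
- pA, pB = mortality in A and B
- The Introduction gives 30-day mortality of 0.6% to 4% across international studies. That range is used only to bound plausible values. It is not a spread between specialties, and the documents give no specialty rates.

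**1. No selection within A (true ratio 1.00).** Recruited patients have mortality pA. Everyone else has

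p0 = [s(1−r)·pA + (1−s)·pB] / [s(1−r) + (1−s)], and the crude ratio is pA / p0.

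With s from 0.4 to 0.6, r of 0.2 or 0.5, and pA = 0.6% against pB = 2% or 4%, the extremes are:
- s = 0.4, r = 0.5, pB = 4%: p0 = (0.2×0.006 + 0.6×0.04)/0.8 = 3.15%; ratio 0.6/3.15 = **0.19**
- s = 0.6, r = 0.2, pB = 2%: p0 = (0.48×0.006 + 0.4×0.02)/0.88 = 1.236%; ratio 0.6/1.236 = **0.49**

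Milder pairs with the same s and r:
- 1.0% v 1.5%, s = 0.4, r = 0.5: p0 = (0.2×0.010 + 0.6×0.015)/0.8 = 1.375%; ratio **0.73**
- 2.0% v 2.5%, s = 0.6, r = 0.2: p0 = (0.48×0.020 + 0.4×0.025)/0.88 = 2.227%; ratio **0.90**

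If the recruiting specialty has the higher risk (3% v 1%, equal volumes, 10% to 50% of A recruited), the ratio runs the other way, from 1.54 to 1.80.

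**2. Selection of lower-risk patients within A.** Let k be the true ratio of recruited to non-recruited mortality in A. Then the non-recruited rate is pn = pA / (r·k + 1 − r), the recruited rate is k·pn, and p0 = [s(1−r)·pn + (1−s)·pB] / [s(1−r) + (1−s)].

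With k = 0.50, pA = 3%, pB = 1%, s = 0.5, r = 0.5:
- pn = 0.03/0.75 = 4%; recruited rate = 2%
- p0 = (0.25×0.04 + 0.5×0.01)/0.75 = 2%
- crude ratio = 2%/2% = **1.00**, so a halving is fully masked

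Other cases, equal volumes:

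| pA v pB | True ratio in A | Fraction of A recruited | Crude ratio | Effect |
|---|---|---|---|---|
| 2% v 1% | 0.70 | 10%; 30% | 0.96; 1.03 | masked |
| 1% v 3% | 0.70 | 10% to 50% | 0.35 to 0.34 | exaggerated |
| 2% v 2% | 0.70 | 10% to 50% | 0.71 to 0.78 | little changed |
| 2% v 2% | 0.50 | 10% to 50% | 0.51 to 0.60 | little changed |

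**3. Comparator limited to A.** The ratio is k·pn / pn = k in every scenario, so the within-specialty ratio is recovered.

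**The case against.** **The comparator answers RQ8 as worded.** RQ8 asks about all potentially eligible patients in PQIP hospitals, and a hospital that recruits one specialty is unrepresentative of its eligible surgery. This stands. The comparison should stay, and specialty coverage is a proper finding from it. The difficulty is that the same contrast is also relied on to judge bias in sampling and patient selection.

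**An article may leave stratification to the full plan.** The characteristics are given as examples and no model is stated, so a fuller document may stratify by procedure. That is possible. But the article does fix the comparator, the levels and the interpretation, and those three do not fit together at a hospital that restricts specialties. By contrast, the RQ9 section states risk adjustment and matching of hospitals.

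**The size is assumed.** This stands. The wide ratios come from placing low and high published mortality on two specialties of one hospital, and milder pairs give 0.73 to 0.90. Hospitals recruiting from all specialties are affected only if the fraction recruited differs between specialties.

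**Stronger readings that the documents do not support.**
- A reader might infer that selection within specialty always stays hidden. It does not: it may be masked, exaggerated or almost unchanged, and the accurate statement is that it is not separately identifiable.
- A reader might infer that the hospital-level comparison is too sparse to be useful. That is a separate matter and concerns mortality only. The recruitment count in the Discussion is interim, the target is 70,000, and age, comorbidity, deprivation, readmission and length of stay are compared as well.
- A reader might infer that every outcome estimate rests on RQ8. The plan also has case-mix adjustment and separate sensitivity analyses for non-response and missing outcomes.

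**Conclusion.** The point holds in a limited form. Where a hospital restricts recruitment to chosen specialties, the RQ8 contrast mixes specialty coverage with selection within specialty, and the second cannot be read from it. Under the assumed rates, coverage alone can give a crude mortality ratio of 0.19 to 0.49 with no selection at all, and a true halving can appear as 1.00. With similar risks across specialties the distortion is small. Size and direction in practice depend on how much specialties differ in risk and how many hospitals restrict recruitment. The documents give neither, so the effect on the national comparison cannot be stated. The change is worth making because the remedy is cheap and the Discussion reports convenience sampling at most sites.

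**What to change.** In the RQ8 section, state two comparisons with separate purposes.

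1. **Coverage.** Keep the comparison with the total eligible cohort, at hospital and national level, and report it as specialty and procedure coverage.
2. **Patient selection.** Add a hospital-level and national comparison limited to the specialties and calendar periods in which each hospital was recruiting, stratified by procedure or standardised to the recruited procedure mix. Name this as the measure of selection, and point the Limitations and Discussion statements on bias to it.

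Report hospital-level differences with intervals, and do not take a non-significant local mortality difference as evidence of representativeness. Partial pooling across hospitals is an option, not a requirement.

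**Cost.** This is a change of analysis wording. The HES extract already planned should serve if it carries procedure and operation date. A record of each site's recruiting specialties and dates is needed, and local estimates will be less precise because the comparator is smaller.
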